### Blinding

The kind of intervention is blinded for the participant and for the follow-up investigator, who was not involved in the surgery. In all study centers, medical postgraduates were employed for the follow-up examination. These raters are explicitly excluded from the screening, randomization, and operative procedure. The randomization list is kept locked in the operating room and is only available to the trial leaders and the surgeons for the process of randomization. After enrollment, only a running number on the CRFs will identify the participant’s position in the list. The rater only has access to the CRFs and not to the randomization list. Adherence to chronological randomization by the list will be monitored by an executive study center. The operation record will only include information about participation in the trial but will not include information about dedicated group. Unblinding is only permitted after dropout or after completion of the trial and can only be performed by the trial leaders.

Figure 1 shows the study flowchart.

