### Randomization

Finally, the enrolled participants will be randomized in a 1:1 ratio by alternating lists in the operating room to primary microsurgical repair with the additional use of a chitosan nerve tube or direct tension-free microsurgical repair of the nerve alone. Final enrollment and randomization following a fixed scheme will be performed by experienced surgeons who are not involved in the screening or follow-up. The CRFs will be accomplished for follow-up.

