### Follow-up

During follow-up, the prepared CRFs will be used by the rater. These CRFs will already include age, gender, profession and current activity, mechanism of the accident, handedness, medical history concerning the hands, date and time of injury, injured side, injured finger, injured nerve, concomitant trauma, and distance from lesion to finger pulp.

Follow-up examinations will be performed after 3, 6, 12, and 24 months. The parameters described below will be measured at 3, 6, 12 and 24 months. Each assessment will take approximately 45 min. In all study centers, medical postgraduates have been employed for the follow-up examination. These raters are explicitly excluded from the screening, randomization, and operative procedure.

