#### Appearance of neuroma

The existence of a neuroma will be assessed by local percussion of the injured nerve site. Electrifying pain will be valued as suspicious for a neuroma. These findings will be verified by neurosonography (linear device, 14 MHz frequency). A final data report will include the count of clinical suspicious neuroma and the count of verified neuroma by sonography. The appearance of neuroma will be a secondary endpoint.

Table 1 summarizes study outcome measures.

**Table 1 Tab1:** Study outcome measures

Item	Outcome measurement [unit]	Time point of measurement	Primary/secondary outcome parameter?
Tactile gnosis**	Static 2-point-discrimination [mm]	at 6 months postoperatively**	primary**
Tactile gnosis**	Static 2-point-discrimination [mm]	at 3, 12, and 24 months postoperatively**	secondary**
Sensory re-innervation	Semmes Weinstein method [grading]	at 3, 6, 12, and 24 months postoperatively	secondary
Disabilities in activities of daily living	DASH questionnaire [score]	at 3, 6, 12, and 24 months postoperatively	secondary
Grip strength	Jamar dynamometer [kg; percentage of contralateral side]	at 3, 6, 12, and 24 months postoperatively	secondary
Motion	Total active range of motion [degree]	at 3, 6, 12, and 24 months postoperatively	secondary
Pain, cold intolerance, hypersensitivity	Visual analog scales [points out of ten]	at 3, 6, 12, and 24 months postoperatively	secondary
Appearance of neuroma	Clinical examination and sonography [count]	at 3, 6, 12, and 24 months postoperatively	secondary

** Tactile gnosis measured by static two-point-discrimination 6 months postoperatively will be considered as the primary outcome parameter. Tactile gnosis** measured by the static two-point discrimination at 3, 12, and 24 months postoperatively will be considered as the secondary outcome parameters

In addition, adverse events (any type of revision surgery, incidence of postoperative hematoma, deep wound infections, disturbances of scar formation such as hypertrophic or instable scars) will be recorded during the hospital stay (approximately 5 days) and retrospectively in the follow-ups. Revision surgery of one affected site will be considered as an adverse event even in cases of multiple nerve injuries. Furthermore, the number of pre- and post-randomization dropouts will be registered and analyzed in a descriptive statistic.

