## Discussion

Standard therapy for traumatic sensory nerve lesions of the hand includes a direct tension-free microsurgical repair for lesions without a gap and autologous nerve grafting from another body region for lesions with a gap [6]. Alternatively, nerve gaps are increasingly reconstructed using nerve tubes to prevent donor site morbidity. A recent meta-analysis shows good and excellent clinical results for this approach [14]. However, prospective controlled single trials are still lacking, and hardly any systematic comparison of standard treatment and the use of nerve tubes are available [14]. The proposed study will compare standard treatment and the use of nerve tubes in a prospective controlled trial setting. Some hand surgery departments also use nerve tubes in addition to a direct nerve suture for lesions without a gap in hopes of improving the results, but such an effect has not yet been proven. Therefore, the major study objective of this trial will be to answer the question of whether the additional use of a chitosan nerve tube in primary microsurgical repair of traumatic sensory nerve lesions of the hand without a gap will improve the recovery of sensitivity. The results will have a direct implication on this common, but as of yet scientifically unproven, practice. A potential study limitation is an example of risk of selection bias because of the quasi-randomization method of using alternating lists. This limitation is due to the emergency surgery setting of the study. Of course, the determined power of 80 % power does also come along with a risk for type II errors of 20 %, but that is conventional for most medical trials. In addition, there is experimental evidence that the use of a chitosan nerve tube may improve functional outcome and reduce the incidence of a painful neuroma [7–11, 24, 25]. The proposed study will test the chitosan-based implant in a clinical setting. If we obtain promising results, we will expand the use of the chitosan nerve tube to use in further studies for traumatic sensory nerve lesions of the hand with a gap as an alternative to autologous nerve grafting and for traumatic nerve lesions of the forearm that include motor axons and therefore have an even more significant burden of disease.

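### Rater blinding is not secured: the follow-up CRF carries the list position, and under alternating allocation one known assignment would reveal the rest of that list

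*Protocol article*

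**What the plan says.** Four statements in the protocol article bear on this point.

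- **Allocation (Randomization).** Participants are "randomized in a 1:1 ratio by alternating lists in the operating room". The same section adds: "Final enrollment and randomization following a fixed scheme will be performed by experienced surgeons". The Discussion calls the method quasi-randomization. The Blinding section says that the executive study centre monitors whether the list is followed chronologically.
- **Identifier (Blinding).** After enrolment, "only a running number on the CRFs will identify the participant’s position in the list".
- **Rater's access (Blinding, Follow-up).** "The rater only has access to the CRFs and not to the randomization list". Under Follow-up: "During follow-up, the prepared CRFs will be used by the rater". These CRFs already hold the date and time of injury, among other items.
- **Unblinding (Blinding).** The trial leaders, and only they, may unblind after a dropout or once the trial is complete.

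The Discussion concedes a "risk of selection bias because of the quasi-randomization method of using alternating lists". It says nothing about what alternation does to rater blinding.

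**The concern.** Withholding the list blinds the rater only if nothing else the rater sees can stand in for it. Here the CRF number is the list position. If the arms alternate, the position's parity is the arm, up to one unknown: which arm is odd. A single disclosed allocation settles that unknown for the whole list.

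The primary outcome, static 2PD at 6 months, is applied by the rater. The rater narrows the distance between two points until the participant reports one, so expectation could affect the result. If the rater could infer the arm, detection bias would act directly on the primary comparison. The planned analysis of covariance, with centre as factor and lesion-to-pulp distance as covariate, could not remove it, because parity separates the arms within each centre.

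**Working it through.** **1. The plan's own figure.** Inputs from Sample size/power calculation: SD 3 mm, difference 2 mm, two-sided level 0.05, power 80%. The two-sample t-test gives 36.3 per group, rounded up to 37, with power 80.8% at 37. The stated 37 is reproduced and does not change under this point. Randomizing 50 per group allows for a loss of 1 − 37/50 = 26%, so dropouts during follow-up are foreseen.

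**2. What one known allocation reveals.** Planned centre sizes are 50, 25 and 25. I assume one list per centre, inferred from the list being kept in the operating room. The rule is to predict every other allocation from one known allocation and odd/even position. The share predicted correctly (simulation, 10,000 runs per cell) is:

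| Sequence | List of 25 | List of 50 |
|---|---|---|
| Strict alternation | 100% (24 of 24) | 100% (49 of 49) |
| Simple randomization | 50.0% | 50.0% |
| Random permuted blocks of 4 and 6 | 50.3% | 50.2% |

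**3. What a biased rater could do to type I error.** The protocol gives no figure for rater bias, so the shifts below are assumptions. With no true effect and 37 per group:

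- SE of the difference = 3 × √(2/37) = 0.697 mm.
- Noncentrality = shift / 0.697, referred to a two-sided 5% t-test with 72 degrees of freedom.

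| Shift averaged over the whole trial | Noncentrality | Type I error |
|---|---|---|
| 0.125 mm | 0.179 | 5.4% |
| 0.25 mm | 0.358 | 6.4% |
| 0.5 mm | 0.717 | 10.9% |
| 1.0 mm | 1.434 | 29.3% |

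**4. Matching the shift to the mechanism.** A leak at one centre affects 25 or 50 of 100 participants. A 0.5 mm bias there averages 0.5 × 25/100 = 0.125 mm or 0.5 × 50/100 = 0.25 mm over the trial, so type I error is 5.4% to 6.4%. Conversely, a trial-wide 0.5 mm shift arising from one centre of 25 would need 0.5 / 0.25 = 2 mm of bias there, which equals the whole assumed treatment effect. The 11% and 29% figures therefore need bias in the same direction at all centres, or a very large bias at one.

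**5. Would a new code alone be enough?** Injury must fall within 72 hours before inclusion. With recruitment over 12 months, a centre enrolling 25 has one participant every 365/25 = 14.6 days on average, and a centre enrolling 50 has one every 365/50 = 7.3 days. Both intervals exceed 3 days, so a rater who sees the injury date and time can largely rebuild the list order without the running number.

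**The case against.** The strongest reply has three parts.

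- **The pattern is inferred.** The protocol never states A-B-A-B. Another fixed pattern would need more than one disclosure. One list per centre is also inferred; a common list would widen the reach, not narrow it. This stands as a condition on the conclusion, although a fixed scheme of alternating lists, described as quasi-randomization, is most naturally read as strict alternation.
- **The number alone reveals nothing.** Someone must leak an allocation, and the protocol has real guards: the list is locked, raters are excluded from screening, randomization and surgery, the operation record omits the group, and only the trial leaders may unblind. Nothing says that raters are told the allocation of a dropout. This also stands. A reader might infer that the stated double blinding fails by design; the text supports only that it is not secured.
- **Other leak routes are speculative.** A reader might infer that neuroma sonography from 3 months would show the tube. The protocol does not say that the tube is visible on ultrasound, or that the 2PD rater performs or sees the scan. The scan is described as a check on clinically suspicious sites: "These findings will be verified by neurosonography (linear device, 14 MHz frequency". Sonography is therefore no evidence of unblinding.

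The admission of selection bias does not answer the point. Selection bias concerns who is enrolled; this concerns who measures the outcome.

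**Conclusion.** The point holds as a conditional design weakness. The protocol bars the rater from the list but gives the rater the list position, under a scheme in which position most likely determines the arm. If alternation is strict, one disclosed allocation reveals 100% of the others on that list, against about 50% under a random sequence.

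The effect on the primary test cannot be derived from the protocol, because it depends on an unknown rater bias. With 0.5 mm of bias at a single centre the inflation is slight (5.4% to 6.4%). It reaches about 11% or 29% only if the shift averages 0.5 or 1.0 mm over the whole trial. Those larger figures should not be read as the expected result of one leak. What justifies acting is that the weakness touches the primary endpoint of a trial described as double-blind, and most of the repair is cheap.

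**What to change.** 1. Label follow-up CRFs with a random code that carries no information on order or arm. Keep the key linking code to list position locked with the allocation list.
2. Keep the date and time of injury off the pages the rater uses; otherwise the order can be rebuilt.
3. Do not disclose dropout allocations to raters while follow-up is still running.
4. At each visit, record the 2PD before any neuroma sonography. The surgical team should not take over the scans: the protocol excludes surgeons from follow-up, and it would unblind the neuroma endpoint.
5. For participants still to be enrolled, preferably replace alternation with a concealed computer-generated random sequence by centre. For them, this removes the inference from position altogether. Participants already allocated by alternation still need steps 1 to 3.
6. If alternation is kept, state the pattern and name the residual risk to rater blinding as a limitation, alongside the selection bias already conceded.

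Cost: minor relabelling, separation of some CRF pages and a line in the rater instructions. Step 5 also needs a sequence to be generated and concealed at each centre. The sample size is unaffected.

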**Fig. 1 Fig1:**
[figure not shown]
Study flowchart

### Participants

All individuals with a fresh traumatic wound of the hand and with the clinical suspicion of traumatic sensory nerve lesions of the hand without a gap will be consecutively screened for eligibility during the preoperative and intraoperative periods.

Preoperative inclusion criteria are as follows:Clinical suspicion of traumatic sensory nerve lesions of the hand without a gap (lesion from the distal area of the carpal tunnel to the end finger joint with complete loss of a nerve-specific receptive field of the finger).Age between 18 and 67 years.Trauma occurred in the previous 72 h.Signed informed consent.

Preoperative exclusion criteria are as follows:Amputated or avascular fingers.Infection of the wound.Known pre-existing impaired sensibility of the injured finger or the opposite side.Allergy to chitosan.Pregnancy.Known immunodeficiency.Participation in other trials.

Intraoperative inclusion criteria are as follows:Verification of a traumatic sensory nerve lesion of the hand without a gap.Nerve can be sutured in end-to-end fashion.

Intraoperative exclusion criteria are as follows:Avascular fingers.Multiple nerve lesions, which cannot be randomized uniformly.Nerve injuries with a gap.

### Outcomes

The primary study objective is the recovery of sensitivity. The assessment will follow the guidelines developed by Rosén [19]. Recovery of sensibility will be assessed by static two-point discrimination (tactile gnosis) and the Semmes Weinstein method (sensory re-innervation). The static two-point discrimination (2PD) after 6 months will be the primary outcome parameter. The 2PD does characterize the sensory capability of the injured finger and is a standard method used in the past for clinical assessment of a variety of artificial nerve tubes [14]. The distance between the lesion and the finger pulp will be attributed in the statistical analysis.

Sensory re-innervation, DASH-score, grip strength, total active range of motion, pain, cold intolerance and hypersensitivity, and the appearance of neuroma will be secondary outcome parameters.

All outcome parameters are frequently used in hand surgery research.

### Interventions

Surgery will be performed in plexus anesthesia or under general anesthesia, depending on the individual’s request and anesthesiologist’s decision, with the use of a tourniquet in a bloodless field. The wound first will be cleaned by flushing and surgical debridement and then explored via Brunner’s incisions [20] using loupes. The injured nerve will be inspected and checked for intraoperative eligibility. Final enrollment and randomization is carried out intraoperatively. Further treatment depends on the dedicated group. If more than one nerve is injured, all the nerves of one individual will be treated in the same fashion. The kind of intervention is blinded for the participant.

#### Experimental group

Participants who are allocated to the experimental group will be treated with an additional chitosan nerve tube. The injured nerve will be exposed and neurolysed for a distance of 2 cm on each side of the lesion. From this point forward, a microscope will be used. The injured ends of the nerve will be sparingly freshened. The chitosan implant will be pre-soaked for 10 minutes in saline. Afterward, the implant (with a length of 1 cm and an inner diameter of 2.1 mm) will be imposed on the proximal nerve stump. A complete tension-free epineural coaptation of the nerve ends will follow, using several 9–0 USP (United States Pharmacopoeia-System) nylon micro-sutures (German Sutures SAS, La Barbiniere, Beaurepaire, France).

Finally, the nerve tube will be positioned at the site of the suture and fixed to the epineurium with a single stitch on each side using a 9–0 USP (United States Pharmacopoeia-System) nylon micro-suture. The use of the chitosan-based nerve tube is already an authorized and CE-certified German medical product (Reaxon® Nerve Guide, Medovent, Mainz, Rheinland-Pfalz,  Germany)

#### Active comparator group

Participants who were allocated to an active comparator group will be treated by standard treatment without using an additional chitosan nerve tube. The injured nerve will be exposed and neurolysed for a distance of approximately 2 cm on each side of the lesion. A microscope will be used from this point onward. The injured ends of the nerve will be sparingly freshened. A tension-free epineural coaptation of the nerve ends using several 9–0 USP (United States Pharmacopoeia-System) nylon micro-sutures will complete the nerve repair (German Sutures SAS, La Barbiniere, Beaurepaire, France).

Other concomitant injuries will be treated independently of the study protocol in the same session.

### Follow-up

During follow-up, the prepared CRFs will be used by the rater. These CRFs will already include age, gender, profession and current activity, mechanism of the accident, handedness, medical history concerning the hands, date and time of injury, injured side, injured finger, injured nerve, concomitant trauma, and distance from lesion to finger pulp.

Follow-up examinations will be performed after 3, 6, 12, and 24 months. The parameters described below will be measured at 3, 6, 12 and 24 months. Each assessment will take approximately 45 min. In all study centers, medical postgraduates have been employed for the follow-up examination. These raters are explicitly excluded from the screening, randomization, and operative procedure.

#### Tactile gnosis: static two-point discrimination (2PD)

The ability of perception of either one or two points of touch will be assessed using a compass (NCD Medical/Prestige, Los Angeles, CA, USA). Participants will sit in front of the rater with the dorsum of the hand on the table. Test will be performed on the halves of finger pulps with preoperatively failed nerve-specific receptive fields and on the correlating finger pulps of the contralateral hand. Pressure is defined by self-weight of the compass (10 g). Two points will be applied in a longitudinal direction with decreasing distance between them until they are perceived as one point. Final distance (in mm) will be the final value. The 2PD measured at 6 months will be the primary outcome parameter; the other values measured at 3, 12 or 24 months will be regarded as secondary outcome parameters.

#### Sensory re-innervation: Semmes Weinstein method

A monofilament is pressed against the halves of the finger pulps with preoperatively failed nerve-specific receptive fields and on the correlating finger pulps of the contralateral hand starting with the thinnest filament. Depending on the response, thicker ligaments are applied until the participant feels the pressure. Six kit monofilaments (Patterson Medical, Warrenville, IL, USA) will be used. Value is measured in grades as follows:0not testable1filament 6.65 = perception of deep pressure2filament 4.56 = no protective sensation3filament 4.31 = diminished protective sensation4filament 3.61 = diminished perception of light touch5filament 2.83 = normal perception of light touch

The sensory re-innervation measured by the Semmes Weinstein method is a secondary outcome parameter.

#### Disabilities of the arm, shoulder, and hand (DASH)

Individuals will self-report their disabilities in activities of daily living by using a DASH (disabilities of the arm, shoulder, and hand) questionnaire [21] in its validated German version [22]. The questionnaire consists of 30 items regarding the requirements of daily life. Optional sport and music modules also exist that are not part of the scoring system. Individuals will assess each item using a scoring system with a range between 1 (no problem with the activity) and 5 (activity is not possible any more). Which hand is used for the activity is not relevant. The assigned values for all completed responses are simply summed and averaged, producing a score out of five. This value is then transformed to a score out of 100 by subtracting one and multiplying by 25, resulting in a DASH score range of 0 to 100. A higher score indicates greater disability. The disabilities of the arm, shoulder, and hand questionnaire (DASH) is a suitable indicator for the burden of the disease by handicaps of the hand [21]. *The DASH*-*score* will be a secondary endpoint.

#### Grip strength

Grip strength will be measured with a Jamar dynamometer (Sammons Preston Inc., Bolinbrook, IL, USA) in stage II. Participants will sit in front of the rater with elbows close fitting to the body and wrists in neutral position. Participants will be requested to press the dynamometer as hard as they can. Three trials with each hand will be carried out. The highest trial will be valued and will be compared with the uninjured hand. Grip strength measured as percentage compared to the contralateral hand will be a secondary endpoint.

